### 2.7. Outcomes

The primary outcome is to evaluate the effects of complex EVAR of para-renal and TAAA on coagulation with respect to von Willebrand factor (vWF), factors VIII and XI, D-dimers, fibrinogen, and Adamts-13 levels and on platelet activation (multiplate).

Perioperative laboratory tests will be performed according to institutional guidelines. These include a complete blood count, conventional coagulation tests, and kidney and liver function tests. In addition, the following parameters will be determined: vWF, factors VIII and XI, D-dimers, fibrinogen, Adamts-13, platelet activation (multiplate), and high-sensitivity troponin (hs-cTNT). The blood samples will be taken at three points in time: preoperatively before induction to general anesthesia, early postoperatively (1st postoperative day), and late postoperatively (3rd–4th postoperative day). The anti-Xa value, correlated to the weight and the dose of the anticoagulant, will also be determined in order to rule out an anticoagulant effect on the laboratory tests.

MINS, MACE, AKI, PIS, implant failure, and death from any cause during hospitalization were defined as secondary outcomes. MACE, implant failure (including secondary sac rupture, graft explantation, type 1 or 3 endoleak or major mitigation of the stent grafts), and death from any cause at 1, 3, 6, and 12 months postoperatively were also defined as secondary endpoints [21].

MINS is defined as postoperative hs-cTNT concentration 20 to 65 ng/L with an absolute change of >/=5 ng/L or any postoperative absolute value >/=65 ng/L [22,23].

MACE is defined as myocardial infarction (any clinical symptom associated with an acute coronary syndrome and/or any new electrocardiographic sign or high-sensitivity troponin elevation), arrhythmia (any event of atrial or ventricular tachycardia with more than 90 pulses per minute or any episode of bradycardia of less than 50 pulses per minute), and stroke (any transient ischaemic attack, any stroke: major or minor according to Rankin Score) [24].

PIS is defined as the presence of at least two of the systemic inflammatory response syndrome (SIRS) criteria, including fever >38 °C and leucocytosis >12,000/μL and obvious clinical or biochemical sign of infection (negative urine and blood cultures and chest X-ray) [24].

AKI is defined according to the RIFLE criteria (Risk, Injury, Failure, Loss of kidney function, and End-stage kidney disease), as a twofold increase in serum creatine or >50% decrease in GFR (estimated using the Cockcroft–Gault equation) [24].

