### 1.3. Objectives

(1)To evaluate the early (postoperative day one) and late (postoperative day 3 or 4) effects of complex EVAR of para-renal and thoraco-abdominal aortic aneurysms on coagulation, with respect to von Willebrand factor (vWF), factors VIII and XI, D-dimers, fibrinogen, Adamts-13 levels, and platelet activation, in patients undergoing complex para-renal and thoraco-abdominal aortic aneurysm repair (primary endpoint);(2)To record the incidence of myocardial injury after non-cardiac surgery (MINS), major adverse cardiovascular events after non-cardiac surgery (MACE), acute kidney injury (AKI), post-implantation syndrome (PIS), and death from any cause during hospitalization;(3)To record the incidence of MACE, implant failure, or death from any cause at 30 days and 3, 6, and 12 months postoperatively.

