### 2.3. Study Schedule

Preoperatively and before induction to general anesthesia, the preoperative data, including demographics (age, gender, body mass index), American Society of Anesthesiologists physical status (ASA PS), any comorbidities and administrated drug therapy, smoking status and alcohol intake, the size of aneurysm, the type of graft used, and baseline liver and renal function will be recorded. In addition, a complete blood count, conventional coagulation tests, kidney and liver function tests, vWF, factors VIII and XI, D-dimers, fibrinogen, Adamts-13, platelet activation (multiplate), and high-sensitivity troponin will be obtained. The anti-Xa value will also be determined in order to rule out an anticoagulant effect on the laboratory tests.

At the first postoperative day, the duration of surgery and the possible occurrence of MINS, MACE, AKI, and PIS will be recorded, while a complete blood count, conventional coagulation tests, kidney and liver function tests, vWF, factors VIII and XI, D-dimers, fibrinogen, Adamts-13, platelet activation (multiplate), and high-sensitivity troponin will be obtained. The anti-Xa value will also be determined in order to rule out an anticoagulant effect on the laboratory tests.

At the 3rd or 4th postoperative day, based on the date of discharge, the length of hospitalization, the number of transfusion units, and the possible occurrence of MINS, MACE, AKI, and PIS will be recorded. In addition, a complete blood count, conventional coagulation tests, kidney and liver function tests, vWF, factors VIII and XI, D-dimers, fibrinogen, Adamts-13, platelet activation (multiplate), and high-sensitivity troponin will be obtained from a peripheral vein. The anti-Xa value, correlated to the weight and the dose of the anticoagulant, is also determined in order to rule out an anticoagulant effect on the laboratory tests.

At 1, 3, 6, and 12 months postoperatively, MACE, implant failure (including secondary sac rupture, graft explantation, type 1 or 3 endoleak, or major mitigation of the stent grafts), and death from any cause will be recorded. The study plan and data collection are summarized in Figure 1.

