### 2.6. Standard Perioperative Care

Perioperative care will be provided in accordance with institutional guidelines and the updated Clinical Practice Guidelines on the Management of Abdominal Aorto-iliac Artery Aneurysms [19]. All patients will be treated by the same surgical and anesthesiologic team in a fully equipped operating theatre under general anesthesia. Intravenous induction to general anesthesia will be achieved with propofol and maintenance with desflurane and dexmedetomidine. In addition to standard monitoring (electrocardiogram, blood pressure, and pulse oximeter), depth of anesthesia, invasive blood pressure, and goal-directed fluid-therapy monitoring will be applied. Every effort will be made to follow the selection criteria recommended by the stent graft manufacturer. However, the final decision will be made by the treating surgeon.

Preoperatively, patients will be treated with 100 mg of aspirin once daily for at least 5 days. If the patient has been treated with clopidogrel, this will be switched to aspirin preoperatively for 10 days [20]. Postoperatively, patients will receive 100 mg of aspirin if there is no bleeding and 75 mg of clopidogrel if there is no neurological dysfunction due to spinal ischemia and dual antiplatelet therapy (DAPT, aspirin 100 mg and clopidogrel 75 mg) from the next day. If the patient has been treated with anticoagulants, these will be discontinued preoperatively in accordance with the ACCP guidelines and resumed on postoperative day 1 or 2, depending on hemostasis [20]. In this case, patients will be treated preoperatively with aspirin 100 mg once daily for 5 days, and aspirin will be continued postoperatively.

Systemic heparinization of the patient will be achieved with 5000 units of unfractionated heparin intraoperatively. One hour after the first administration of heparin, and every 30 min thereafter, the activated clotting time (ACT) will be measured. The intraoperative ACT target is set at 200–300 s.

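### The arrhythmia part of MACE is triggered by heart rate alone, so an unchanged pre-existing arrhythmia can be counted as a postoperative event

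*Protocol article*

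**What the plan says.** Section 2.7 builds MACE from infarction, arrhythmia and stroke. The arrhythmia part has two triggers: "any event of atrial or ventricular tachycardia with more than 90 pulses per minute" and "any episode of bradycardia of less than 50 pulses per minute". A rate limit is the only condition on either.

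The infarction part of the same definition accepts "any new electrocardiographic sign or high-sensitivity troponin elevation", so the electrocardiographic sign must be new. For troponin between 20 and 65 ng/L, the MINS definition asks for a value "with an absolute change of >/=5 ng/L". AKI is defined by a rise in creatinine or a fall in GFR.

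Section 2.5 and Table 2 do not exclude patients with a known arrhythmia, and enrolment is consecutive. Section 2.6 provides for patients on long-term anticoagulation: "If the patient has been treated with anticoagulants, these will be discontinued preoperatively". At baseline, section 2.3 records "any comorbidities and administrated drug therapy".

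Section 1.3 makes incidence the objective, first in hospital and then in follow-up: "To record the incidence of MACE, implant failure, or death from any cause at 30 days and 3, 6, and 12 months postoperatively".

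**The concern.** An incidence counts events that arise after the starting point, here the operation. A definition that looks only at the postoperative rate cannot tell a rhythm that began or worsened after surgery from one that was already there. A patient with, for example, long-standing atrial fibrillation who runs at 91 per minute on the ward meets the definition even if the preoperative rate was the same. A patient whose rate was already below 50 per minute before surgery meets the other trigger.

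MACE is a secondary outcome in hospital and at 1, 3, 6 and 12 months. Section 3.1 states that there is one group, so no comparator carries the same misclassification and offsets it. The absolute rate is the result that readers will take away, and any error of this kind moves it in one direction.

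**Working it through.** The plan states no expected MACE rate, so there is no figure to reproduce. The check is a comparison of the text, followed by an illustration of scale.

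**Text comparison**

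| Item in 2.7 | Reference to the preoperative state |
|---|---|
| Infarction, electrocardiographic sign | Must be new |
| MINS, 20 to 65 ng/L | Change of at least 5 ng/L |
| MINS, 65 ng/L or more | None |
| AKI | Twofold rise in creatinine or a fall in GFR of more than 50% |
| Arrhythmia, above 90 per minute | None |
| Arrhythmia, below 50 per minute | None |

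No other section adds a new-onset or change condition to the arrhythmia part, and the eligibility criteria do not remove the patients to whom the gap applies.

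**Illustration of scale**

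From the document: planned N = 65 (section 3.1). Assumed, because the document gives no figures:

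- p, the share of patients with a pre-existing tachyarrhythmia: 5–20%
- q, the share of those who exceed 90 per minute at least once after surgery: 25–75%
- i, the incidence of MACE arising after surgery: 5–20%, taken as independent of p and q

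Formulas:

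- Patients meeting the arrhythmia part through a pre-existing rhythm = 65 × p × q
- Recorded MACE rate = i + p × q × (1 − i)
- Share of recorded MACE due to the pre-existing rhythm = p × q × (1 − i) ÷ recorded rate

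| p | q | i | Patients of 65 | Recorded rate | Share |
|---|---|---|---|---|---|
| 5% | 25% | 20% | 65 × 0.0125 = 0.8 | 0.20 + 0.0125 × 0.80 = 21.0% | 0.010 ÷ 0.210 = 5% |
| 10% | 50% | 10% | 65 × 0.05 = 3.25 | 0.10 + 0.05 × 0.90 = 14.5% | 0.045 ÷ 0.145 = 31% |
| 20% | 75% | 5% | 65 × 0.15 = 9.75 | 0.05 + 0.15 × 0.95 = 19.25% | 0.1425 ÷ 0.1925 = 74% |

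The first and last rows are the extremes of the assumed grid for the patient count and the share. Two features limit these figures. They treat every excursion above 90 per minute in a patient with a known arrhythmia as misclassified, although some of those excursions would be real postoperative changes; in that respect they overstate. They also leave out the bradycardia trigger, which has the same gap.

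**The case against.** The strongest reply is that the wording already points to something that happens after surgery: the definition speaks of an event or an episode, and the objective speaks of incidence. Atrial fibrillation is never named, and the indication for anticoagulation in 2.6 is not given, so the presence of affected patients is an inference. The definition also cites a source that is not at hand, and a condensed article may leave adjudication to the full protocol.

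Part of this stands. The text permits the broad reading without compelling it, and eligibility of anticoagulated patients is only compatible with known arrhythmia in the cohort. But the article does not leave the matter open: it gives an operative rule with numerical limits, and a rate excursion in a known arrhythmia satisfies that rule. Two assessors could classify the same patient differently.

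Three stronger readings are tempting, and the documents do not support them.

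- *The MACE rate measures the baseline prevalence of atrial fibrillation.* It does not. A known arrhythmia that stays at or below 90 per minute, and not below 50, is not counted, and some patients who pass a limit will have changed since surgery.
- *Any association between MACE and the coagulation markers would be spurious.* This does not follow. Infarction and stroke are untouched, anti-Xa is measured at each sampling point to rule out an anticoagulant effect (section 2.3), and section 3.2 specifies no analysis of MACE against the markers. Confounding through anticoagulant use is possible, no more.
- *The same patient will be counted again at each follow-up visit.* The article does not say how an earlier event is handled later.

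**Conclusion.** The point holds in a limited form. As written, the arrhythmia part of MACE can count an unchanged pre-existing rhythm as a postoperative event, while neighbouring definitions in the same section mostly ask for something new or changed. The direction is upward if at least one such patient is enrolled, crosses a rate limit and has no other MACE.

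The size cannot be fixed from the documents. The range of about 1 to 10 patients in 65 rests wholly on the assumed prevalence and the assumed share above 90 per minute, and serves only to show that the effect could be anything from negligible to a large part of the recorded rate. Because MACE is a secondary outcome, the primary coagulation outcome and the sample size are not affected. The definition should be amended before MACE events are classified.

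**What to change.** In section 2.7, state that an arrhythmia counts towards MACE only if it is new, or changed (recurrent or worsened), relative to the preoperative record. Including recurrence and worsening matters: a rule that dropped every rhythm documented before surgery would also lose a genuine postoperative ventricular tachycardia in a patient with an earlier episode, and would replace over-counting with under-counting.

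Apply the same rule in hospital and at 1, 3, 6 and 12 months. Report the arrhythmia component separately from infarction and stroke, and list rate episodes in unchanged known arrhythmia outside MACE, so that no observation is lost.

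This changes the classification of outcomes, not care. It costs one added phrase and one extra line in the results table. The preoperative rhythm has to be read from the comorbidity record that section 2.3 and Table 3 already collect, since neither names rhythm as an item of its own. The reported MACE rate may be somewhat lower.

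### The definition of post-implantation syndrome asks for a sign of infection in the clause whose bracket asks for a negative infection work-up, so the recorded incidence would be wrong if the text is followed

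*Protocol article*

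**What the plan says.** Section 2.7 (Outcomes) of the protocol article lists PIS among the in-hospital secondary outcomes: "MINS, MACE, AKI, PIS, implant failure, and death from any cause during hospitalization were defined as secondary outcomes". The second objective in section 1.3 is to record the incidence of a set of events that ends with "post-implantation syndrome (PIS), and death from any cause during hospitalization".

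The definition is a single sentence in section 2.7 with three parts:

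- The inflammatory part: "PIS is defined as the presence of at least two of the systemic inflammatory response syndrome (SIRS) criteria".
- The named criteria: "including fever >38 °C and leucocytosis >12,000/μL".
- The infection part: "and obvious clinical or biochemical sign of infection (negative urine and blood cultures and chest X-ray".

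The Abstract, sections 2.3, 2.8 and 5, and Table 3 name PIS as something to be recorded or investigated. None of them defines it or corrects section 2.7.

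**The concern.** The infection part is joined to the rest by a plain *and*, with no *no* or *without* in front of it. Grammatically, a patient must show a sign of infection to be classed as having PIS. The bracket attached to the same clause asks for a negative infection work-up, which is how one would show that infection is absent. The two halves point in opposite directions.

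What is at stake is the PIS incidence, which is part of a stated objective. Someone classifying patients from the published text would not count a patient with fever, leucocytosis, no sign of infection and a clean work-up, although that is the patient the bracket describes. A reader of the results could not tell whether the text or its presumed intention had been followed.

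A smaller ambiguity sits in the same sentence. It asks for at least two SIRS criteria and then names fever and leucocytosis after the word *including*. It does not say whether both must be among the criteria met or whether they are examples.

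**Working it through.** The plan gives no figure to reproduce. The check is to treat the definition as a logical AND of its parts and apply it to each possible type of patient.

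The inputs, all from section 2.7, are: (i) at least two SIRS criteria; (ii) a sign of infection, stated without negation; (iii) a negative work-up, from the bracket. Every patient type below is assumed to meet (i).

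| Type | Sign of infection | Work-up | Text as written: (i) and (ii) and (iii) | With negation restored: (i) and not (ii) and (iii) |
|---|---|---|---|---|
| A | absent | negative | not counted | counted |
| B | present | negative | counted | not counted |
| C | present | positive | not counted | not counted |
| D | absent | positive | not counted | not counted |

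Three readings of the text as written follow.

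1. **Sign and work-up are separate conditions.** Only type B is counted: suspected infection that the tests did not confirm. Type A, the sterile SIRS that the bracket points to, is left out.
2. **A negative work-up means that there is no sign of infection.** Conditions (ii) and (iii) then exclude each other, type B is empty, and nobody is counted.
3. **Fever and leucocytosis are themselves the sign of infection.** The intended patients would be counted, but the infection clause would add nothing to the SIRS part. This is not the natural reading.

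On size, let *a* and *b* be the numbers of type A and type B patients among the 65 planned. The incidence that the bracket implies is *a*/65. The text gives *b*/65 under reading 1 and 0 under reading 2. The error is therefore (*b* − *a*)/65 or −*a*/65. The article gives neither *a* nor *b*, nor any PIS or infection rate from which to derive them, so the expression cannot be evaluated. Under reading 1 the error vanishes if *a* = *b*, but then the right number would be reported for the wrong patients.

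The negation settles the A/B problem but not the SIRS ambiguity. A patient who meets two SIRS criteria, only one of which is fever or leucocytosis, qualifies if the named criteria are examples and does not qualify if both are mandatory.

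**The case against.** The strongest reply is that this looks like one dropped word and that the sentence corrects itself. The bracket names the tests that would exclude infection, so a clinician would probably guess the meaning and classify accordingly. PIS is one of several secondary outcomes, and its objective is only to record how often it occurs. The primary outcome (section 2.7), the sample size calculation (section 3.1) and the comparison across time points (section 3.2) do not use it. All of this stands, and it lowers the weight of the point. It does not remove the point: this is the operative rule for a reported outcome, and no other section supplies the correct version.

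A reader might infer three stronger things that the article does not support.

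- *That infected patients in general would be counted as PIS.* The bracket excludes anyone with a positive work-up (type C). At most, suspected but test-negative infections enter.
- *That a number of misclassified patients can be given.* Multiplying 65 by an assumed PIS rate has no anchor in the article. Multiplying 65 by an assumed overall infection rate gives only a ceiling, because the rule also needs at least two SIRS criteria and a negative work-up.
- *That a planned analysis linking the coagulation markers to PIS would be damaged.* Neither section 1.3 nor section 2.7 specifies one. Section 3.2 directs the regression at risk factors for the primary outcome and mentions ROC curves without naming an outcome.

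**Conclusion.** The definition is wrong as written. Followed literally, it omits sterile SIRS and counts either only suspected, test-negative infection or nobody, so the recorded PIS incidence would be wrong. This rests on the wording of one sentence in section 2.7 and on there being no other PIS definition in the article. That a negation was dropped is an inference from the bracket, though a strong one.

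The size of the error is not computable from the document. The damage is confined to the PIS incidence and to any later use of that classification. The primary coagulation endpoint and the sample size of 58, raised to 65, are untouched. Because the bracket signals the intended meaning, this is a correction of modest weight that should be made before PIS is classified. It does not threaten the study's main result.

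**What to change.** In section 2.7, insert *no* before *obvious* in the infection clause so that the clause agrees with its bracket. Leave the requirement for at least two SIRS criteria as it stands; replacing it with fever plus leucocytosis would narrow the definition. Re-check any PIS entries already coded under the published text.

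As a separate and lesser clarification, say whether fever and leucocytosis must both be present or are examples of the two criteria.

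The text change costs one word, plus a short phrase for the clarification. Re-checking should be light if temperature, culture and chest X-ray results can be retrieved. Section 2.8 says that most data come from routine admission documents and the electronic file, which makes this plausible. However, those items are not listed in sections 2.3 or 2.8 or in Tables 3 and 4, so their availability should be confirmed.

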### 2.8. Data Collection

Most of the data will be obtained from the routine admission documents and the electronic patient file. They will be recorded in a password-protected spreadsheet. Basic data collection will include demographics (age, gender, body mass index), ASA physical status, any comorbidities and administrated drug therapy, smoking status and alcohol intake, the size of aneurysm, the type of graft, liver and renal function, the duration of surgery, the length of hospitalization, the number of transfusion units, and the possible occurrence of MINS, MACE, AKI, and PIS. The basic data that will be collected are presented in Table 3.

As far as the laboratory values are concerned, the following parameters will be determined: vWF, factors VIII and XI, D-dimers, fibrinogen, Adamts-13, platelet activation (multiplate), and high-sensitivity troponin. All samples will be taken by puncturing a peripheral vein. The blood samples will be taken at three points in time: preoperatively before induction of general anesthesia, early postoperatively (1st postoperative day), and late postoperatively (3rd–4th postoperative day). The anti-Xa value, correlated to the weight and the dose of the anticoagulant, will also be determined in order to rule out an anticoagulant effect on the laboratory tests. The additional laboratory values that will be collected are presented in Table 4.

